We will conduct a pragmatic cluster-randomised, parallel group, superiority trial to evaluate the efficacy and safety of treatment for LTBI in recent migrants within primary care as compared to treatment in secondary care. The primary objective will be treatment completion (defined as taking at least 90% of antibiotic doses on pill count). The secondary objectives of the trial will assess adherence, acceptance of treatment, the incidence of adverse effects including drug-induced liver injury (DILI), the rates of active TB, patient satisfaction and the cost-effectiveness of treatment.

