### Outcomes

#### Primary outcome –treatment completion

Completion of at least 90% of prescribed therapy as assessed by pill count. Where a patient fails to bring their medication, information will be obtained by patient report. Treatment completion will be assessed at the final patient review, approximately 3 months after treatment is commenced. To avoid bias, an independent researcher, blinded to allocation, will verify treatment completion where there is uncertainty. This outcome is defined for IGRA positive patients who accept treatment.

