#### Secondary outcomes

Proportion of participants completing < 80, 80–89.9, ≥90% of antibiotic dosages based on pill count.Treatment adherence assessed using the five-point adherence questionnaire (MARS5 tool), prescription collection and a point-of-care urine testing for metabolites of Isoniazid (Isoscreen) at monthly intervals.Treatment acceptance assessed by calculating the proportion of eligible patients that accept therapy; this is defined as those initiating treatment and attending TB clinics and community pharmacies on at least one occasion.The number of patients on treatment having adverse events including DILI leading to discontinuation of treatment or hospitalisation. Safety of treatment will be assessed every month by the pharmacist in primary care and by the TB nurse in secondary care.The incidence of active TB occurring within 2 years after enrolment. TB incidence in the intervention and control group will be compared and there will be a sub-group analysis to evaluate the effect of the intervention in those who did or did not complete treatment. This will be performed through matching the study population with the national Enhanced TB Surveillance System, where information on all reported TB cases nationally are recorded.Assessment of patient satisfaction.Evaluation of cost-effectiveness of LTBI treatment in primary care compared to secondary care.

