### Sample size

We predict treatment completion in primary care to improve by 15% compared with secondary care (from 70 to 85%). To detect this difference with 80% power, and 5% significance level, an individually randomised trial would require 268 participants. We planned to conduct our trial in a minimum of 20 GP practices (10 intervention and 10 control), noting that as the number of GP practices increases, the required total sample size of individual participants falls. With 20 practices, we would have needed to adjust for the effect of clustering by increasing the sample size to 780 participants (or 39 patients per practice) assuming an ICC of 0.05. To allow for loss to follow up and treatment non-acceptance we would have inflated the required sample size by 30% to 1014 participants (51 per GP practice). The final number of practices randomised was 34, though as 14 were randomized after the initial phase we expect variability in cluster size reflected by a coefficient of variation of 0.5. Under the same assumptions as before the number of individuals required providing the primary outcome is 442 (221 per arm), inflated due to loss to follow up and treatment non-acceptance to 576 (17 per practice).

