### Analysis

All analyses will be conducted on an intention-to-treat basis. The analysis will include all eligible participants regardless of how well the GP practice followed the study protocol or how well the participant complied with their treatment plan. The analysis will exclude any patients however who have withdrawn from the trial and specified they do not wish their data to be analysed.

Some outcomes are only applicable for certain subgroups. The primary outcome is defined only for patients who accept treatment. Patient satisfaction is only defined for patients who are still under care at 2 months, when the satisfaction questionnaire is administered. The MARS-5 and isoniazid metabolite urine testing adherence measures are only applicable at times when the patient is still taking treatment, i.e. not stopped due to adverse effects or by patient choice/withdrawal from the trial.

The primary outcome will be analysed using a logistic regression model. Results will be reported as odds ratios (OR) for the intervention compared to control with their corresponding 95% confidence intervals (CI) and two-sided *p*-values. The ICC for the primary outcome will be reported. Similarly, across the secondary outcomes treatment effect estimates will be presented with 95% confidence intervals based on regression models, using binary logistic regression, ordinal logistic regression or linear regression as appropriate. Regression models will include random intercept effects for GP practice.

Adjusted effect measures are considered the primary effect measures; unadjusted measures will also be reported. We will adjust the analyses for practice size and number of previous IGRA positives, our stratification factors, and selected pre-determined participant factors considered predictive of treatment completion.

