### Harms

The intervention in this trial is the setting of care. There are no specific anticipated harms associated with allocation within the trial. However, patients in both arms of the trial will be treated for LTBI with a 3-month course of daily Rifinah®. This preparation is licenced for use in the UK and is currently recommended for LTBI [20, 22].

Trial participants will be monitored for adverse events (AEs) and serious adverse events (SAEs) at each monthly review and are asked to undertake a blood test to assess liver function after 2 to 4 weeks of treatment.

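### The planned TB analysis of the intervention effect within completers and within non-completers conditions on the post-randomisation primary outcome, so those two contrasts are not randomised comparisons

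*Protocol article*

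**What the plan says.** In the protocol article, under Secondary outcomes, the active TB item contains two analyses. The first is the arm comparison: "TB incidence in the intervention and control group will be compared". The second follows in the same sentence: "there will be a sub-group analysis to evaluate the effect of the intervention in those who did or did not complete treatment".

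Other sections fix what these words mean:

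- **Intervention.** Under Harms: "The intervention in this trial is the setting of care". It is the randomised allocation, not the drug.
- **Completion.** Under Primary outcome: "Completion of at least 90% of prescribed therapy as assessed by pill count". The end of the Background makes the same quantity the primary objective.
- **Timing.** Under Primary outcome: "Treatment completion will be assessed at the final patient review, approximately 3 months after treatment is commenced".
- **Population.** Under Analysis: "The primary outcome is defined only for patients who accept treatment". Acceptance is itself a secondary outcome observed after practices are randomised.
- **Expected effect of allocation on completion.** Under Sample size: "We predict treatment completion in primary care to improve by 15% compared with secondary care (from 70 to 85" per cent).

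The Analysis section puts every analysis on an intention-to-treat basis. Nothing in the article calls the completion subgroup analysis exploratory or non-causal, or names a method for handling selection after randomisation.

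**The concern.** A subgroup analysis of a randomised effect is sound when the subgroups are fixed before allocation. Here the subgroup is the trial's own primary outcome, which allocation is meant to change. If the trial works as designed, some patients who would be non-completers in secondary care become completers in primary care. The completers in the two arms are then different mixtures of patients, and so are the non-completers.

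There is a second problem. Completion is the main route by which setting could be expected to prevent TB. Holding completion fixed blocks that route, so a real benefit gained through completion would not appear in either subgroup.

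The trial is meant to inform national policy on where latent TB infection is treated. A result presented as the effect of primary care on TB in completers or in non-completers could be read as randomised evidence, which it would not be.

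**Working it through.** **Inputs from the protocol article:** completion 70% (control) and 85% (intervention), 80% power, 5% significance, 268 for an individually randomised trial, 221 per arm providing the primary outcome (all Sample size); two-sided p-values (Analysis). **Not in the documents:** any TB risk. All TB risks below are assumptions.

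**Step 1. Reproduce the plan's figure for the effect on completion.** With p̄ = 0.775:

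n per arm = [1.960·√(2·0.775·0.225) + 0.842·√(0.70·0.30 + 0.85·0.15)]² / 0.15² = 120.5

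With continuity correction: (120.5/4)·[1 + √(1 + 4/(120.5·0.15))]² = 133.5, rounded up to 134, so 2 × 134 = 268. This matches, so the design does rest on allocation moving the subgrouping variable from 70% to 85%.

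**Step 2. Size of the subgroups, taking 221 per arm as stated.**

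| | Control | Intervention |
|---|---|---|
| Completers | 221 × 0.70 = 154.7 | 221 × 0.85 = 187.9 |
| Non-completers | 221 × 0.30 = 66.3 | 221 × 0.15 = 33.2 |

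The difference is 221 × 0.15, about 33 patients per arm. They count as non-completers under control and as completers under the intervention.

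**Step 3. What the subgroup contrasts would estimate.** Assume the patients with a completion status are alike in the two arms and that nobody completes only in secondary care. There are then three types: 70% complete in either setting (A), 15% complete only in primary care (I), 15% never complete (N). Let r be the two-year TB risk without completion, and let completion multiply it by e. Setting acts on TB only through completion.

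- Completers: RR = (0.70·r_A + 0.15·r_I) / (0.85·r_A). The multiplier e cancels.
- Non-completers: RR = r_N / [(r_I + r_N)/2]. This does not involve e.
- Overall: RR = (0.70·e·r_A + 0.15·e·r_I + 0.15·r_N) / (0.70·e·r_A + 0.15·r_I + 0.15·r_N).

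In these formulas the true effect of setting within each completion level is null, so any subgroup RR other than 1 is selection. With e = 0.3:

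| Assumed r_A, r_I, r_N | RR in completers | RR in non-completers | Overall RR | Expected TB cases per 221, control v intervention |
|---|---|---|---|---|
| 2%, 2%, 2% | 1.00 | 1.00 | 0.79 | 2.3 v 1.8 |
| 2%, 3%, 4% | 1.09 | 1.14 | 0.79 | 3.2 v 2.6 |
| 2%, 4%, 4% | 1.18 | 1.00 | 0.74 | 3.6 v 2.7 |
| 2%, 2%, 4% | 1.00 | 1.33 | 0.84 | 2.9 v 2.5 |
| 2%, 4%, 8% | 1.18 | 1.33 | 0.81 | 4.9 v 4.0 |
| 4%, 3%, 2% | 0.96 | 0.80 | 0.80 | 3.5 v 2.8 |

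The fifth row in full: completers (0.70·0.02 + 0.15·0.04)·0.3/0.85 = 0.706% v 0.02·0.3 = 0.600%, ratio 1.18; non-completers 8% v (4% + 8%)/2 = 6%, ratio 1.33; overall 1.80% v 2.22%, ratio 0.81.

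For that row, varying e from 0.1 to 0.5 leaves 1.18 and 1.33 unchanged and moves the overall RR from 0.72 to 0.88.

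**Step 4. Events.** Across these rows the two arms together would yield about 4 to 9 cases. Split by completion, the intervention non-completers would hold about 0.7 to 2.7 cases and the control completers about 0.9 to 1.9.

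**The case against.** The strongest reply is about scope. This is one supplementary analysis of one of seven secondary outcomes. The sound arm comparison is planned in the same sentence, and neither the primary analysis nor the sample size uses the subgroup result. That stands, and it limits the severity. A reader might infer that the TB comparison as a whole loses its randomised basis. The documents do not support that, because the overall comparison does not condition on completion.

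A second reply is that the direction of the bias is not known. That also stands. A reader might infer that the analysis would show primary care as harmful in both subgroups. This happens in two of the six assumed sets above. Another gives 1.00 in both, and another puts both below 1. With so few cases, the likeliest practical result is a table that supports no conclusion. Sparse events are not peculiar to this analysis, however; they limit the overall TB comparison as well.

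A third reply is that the authors may have meant TB incidence by completion status, and that the full protocol or an analysis plan, neither of which is shown, may label it cautiously. Either is possible. But the article states an effect of the intervention in those groups, so this is something stated and not a detail left out. The alternative reading is also a non-randomised comparison.

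Finally, asking whether setting matters beyond completion is a legitimate question. It needs stated causal assumptions, which a plain subgroup split does not supply.

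**Conclusion.** The point holds, at moderate severity. As written, the article plans to estimate the effect of setting on TB within strata of its own post-randomisation primary outcome, among acceptors only. Those two contrasts are not protected by randomisation, and they exclude any benefit that comes through completion. This follows from the article's own definitions and its predicted shift from 70% to 85%; it needs no assumption about TB risk.

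The numerical size does rest on assumptions: the TB risks by type of patient, no direct effect of setting, nobody completing only in secondary care, and acceptors alike across arms. Under those, with overall risk ratios of 0.74 to 0.84 at e = 0.3, the subgroup ratios span 0.96 to 1.18 in completers and 0.80 to 1.33 in non-completers. These figures illustrate the problem and do not forecast the result.

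**What to change.** In the active TB item under Secondary outcomes:

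1. Remove the arm contrast by completion status as an estimate of the intervention effect.
2. Keep the arm comparison of two-year TB incidence in all enrolled patients, and name it as the inferential analysis.
3. If the relation between completion and TB is of interest, report TB incidence in completers and non-completers pooled over arms, labelled observational and descriptive.
4. If the question is whether setting acts beyond completion, replace the subgroup split with a principal-stratum or mediation analysis, state its assumptions, and acknowledge the small number of events.

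Items 1 to 3 change wording only. They need no new data and leave the sample size and the primary analysis as they are. Item 4 is optional and would need additional analysis.

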#### Additional outcomes

Identification of factors associated with treatment non-acceptance and completion using a standardised questionnaire to explore patients’ understanding and knowledge of LTBI.

### Sample size

We predict treatment completion in primary care to improve by 15% compared with secondary care (from 70 to 85%). To detect this difference with 80% power, and 5% significance level, an individually randomised trial would require 268 participants. We planned to conduct our trial in a minimum of 20 GP practices (10 intervention and 10 control), noting that as the number of GP practices increases, the required total sample size of individual participants falls. With 20 practices, we would have needed to adjust for the effect of clustering by increasing the sample size to 780 participants (or 39 patients per practice) assuming an ICC of 0.05. To allow for loss to follow up and treatment non-acceptance we would have inflated the required sample size by 30% to 1014 participants (51 per GP practice). The final number of practices randomised was 34, though as 14 were randomized after the initial phase we expect variability in cluster size reflected by a coefficient of variation of 0.5. Under the same assumptions as before the number of individuals required providing the primary outcome is 442 (221 per arm), inflated due to loss to follow up and treatment non-acceptance to 576 (17 per practice).

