### Missing data

Some patients will inevitably be lost to follow-up, arising primarily because they have withdrawn from treatment. For the primary outcome, a patient who withdraws from treatment without collecting all prescriptions will be classified as having failed treatment. We will impute missing data for those patients that collect all prescriptions but miss the final visit using multiple imputation by chained equations (MICE). A sensitivity analysis will also be performed in this group in which those failing to attend a final visit are assumed to have failed treatment.

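### The stated sample sizes do not share one basis: 268 and 780 need a continuity-corrected formula, and on that formula 442 does not follow for 34 practices with a cluster-size CV of 0.5

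*Protocol article*

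**What the plan says.** All figures are in one paragraph of the protocol article, Methods and design, Sample size.

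- Effect: "We predict treatment completion in primary care to improve by 15% compared with secondary care (from 70 to 85"%).
- Individual randomisation: "To detect this difference with 80% power, and 5% significance level, an individually randomised trial would require 268 participants".
- Twenty practices: 780 participants, 39 per practice, at an ICC of 0.05. No variation in cluster size is mentioned at this step.
- Thirty-four practices: "we expect variability in cluster size reflected by a coefficient of variation of 0.5".
- The resulting target: "Under the same assumptions as before the number of individuals required providing the primary outcome is 442 (221 per arm"), which is then "inflated due to loss to follow up and treatment non-acceptance to 576 (17 per practice").

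The Analysis section promises "corresponding 95% confidence intervals (CI) and two-sided" p-values from a logistic regression with random practice intercepts. The Randomisation section gives 17 practices per arm.

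**The concern.** The natural reading is that effect, power, significance level, ICC and formula carry over from the 20-practice calculation, and that only the number of practices and the CV change. If so, 442 should follow from the method that gives 268 and 780, with CV 0.5 added. It does not. Either the declared allowance for unequal clusters is not in the number, or the formula changed between two sentences that say nothing changed.

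This paragraph is the only justification the article gives for the revised target, and the Abstract repeats 576. Anyone judging later whether the trial was large enough will use the stated 80% power, which at present cannot be tied to one calculation.

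**Working it through.** **Inputs** (Sample size, Analysis and Randomisation sections): 70% v 85%, two-sided 5%, 80% power, ICC ρ = 0.05, k = 10 or 17 practices per arm, CV = 0 or 0.5.

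**Step 1. Base size per arm.** Pooled two-proportion formula:

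n = [1.96 √(2 × 0.775 × 0.225) + 0.8416 √(0.70 × 0.30 + 0.85 × 0.15)]² / 0.15² = 120.5, so 121 per arm (242 in total).

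With continuity correction: n′ = (n/4)[1 + √(1 + 4/(n × 0.15))]² = 133.5, so 134 per arm (268 in total).

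The plan's 268 is therefore the corrected value.

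**Step 2. Clustering.** With design effect DE = 1 + [(1 + CV²)m − 1]ρ, solving k·m = n·DE for the cluster size m gives

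m = n(1 − ρ) / [k − nρ(1 + CV²)],

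rounded up to a whole patient per practice.

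| Base per arm | Practices | CV | m | Total before rounding | Total in whole patients |
|---|---|---|---|---|---|
| 134 (corrected) | 20 | 0 | 127.3/3.3 = 38.58 | 771.5 | 39 × 20 = **780** |
| 121 (uncorrected) | 20 | 0 | 114.95/3.95 = 29.10 | 582.0 | 30 × 20 = 600 |
| 134 | 34 | 0 | 127.3/10.3 = 12.36 | 420.2 | 13 × 34 = **442** |
| 134 | 34 | 0.5 | 127.3/8.625 = 14.76 | 501.8 | 15 × 34 = 510 |
| 121 | 34 | 0 | 114.95/10.95 = 10.50 | 356.9 | 11 × 34 = 374 |
| 121 | 34 | 0.5 | 114.95/9.4375 = 12.18 | 414.1 | 13 × 34 = **442** |

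The plan's 780 is reproduced only on the corrected base. Its 442 is reproduced in two ways: corrected with CV 0, or uncorrected with CV 0.5. No single row type gives 268, 780 and 442 with CV 0.5.

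**Step 3. Power at 442 with CV 0.5.** At m = 13, DE = 1 + (1.25 × 13 − 1) × 0.05 = 1.7625. Effective size is 442/1.7625 = 250.8, or 125.4 per arm, against the stated 268 (134 per arm). Then

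z = [0.15 − c − 1.96 √(0.34875/125.39)] / √(0.3375/125.39) = [0.15 − c − 0.1034] / 0.0519.

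- Uncorrected (c = 0): z = 0.899, power 81.6%.
- Corrected (c = 1/125.39 = 0.0080): z = 0.745, power 77.2%.

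**Step 4. Sensitivity to the design effect.** The milder relative-efficiency adjustment for unequal clusters, with the correction kept, needs about 467 (14 × 34 = 476 in whole patients), again not 442. Power at 442 is then 78.8% corrected and 82.9% uncorrected. An uncorrected calculation with the standard design effect and a t reference on 32 degrees of freedom gives about 80.1%.

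**The case against.** The strongest reply is that 442 is reproducible. The ordinary uncorrected formula, with every input the paragraph states including CV 0.5, gives 13 × 34 exactly, with power near 82%. The planned mixed logistic model uses no continuity correction, so this is arguably closer to the planned test. The article names no formula, and the correction is inferred only from 268 and 780, which belong to a superseded 20-practice plan.

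Much of this stands. A reader might infer that the CV was ignored, or that the trial has only 77% power. Neither is established: across the methods above, power runs from about 77% to 83%, on both sides of 80%. Nor is it a fault in itself that a condensed article names no formula.

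The reply does not rescue the sentence. The uncorrected route abandons the base behind both earlier figures, while the text says that the assumptions are kept. The inference about that base is also firm: two separate figures, 268 and 780, match the corrected formula, and the uncorrected one gives 242 and 600.

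A reader might also fault the step from 442 to 576. The documents do not support that. The section describes a 30% inflation, and 221 × 1.3 = 287.3, rounded up to 288 per arm, is 576. This tolerates a loss of 1 − 442/576 = 23.3%, but nowhere is a 30% loss stated as expected, so no larger total follows. Nor does only refusal of treatment remove information. Although "a patient who withdraws from treatment without collecting all prescriptions will be classified as having failed treatment", the Missing data section imputes the outcome for those who collect every prescription but miss the final visit, and the Analysis section excludes patients who withdraw and do not want their data analysed. Some allowance for loss to follow-up is reasonable.

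**Conclusion.** The paragraph is wrong as written: 268, 780 and 442 cannot all come from one formula once the declared CV of 0.5 is applied. On the basis that yields the first two, 34 practices need about 502 (510 in whole patients), which is 60 more than 442 before rounding, or 13.6%; 442 then gives about 77% power instead of 80%. On the uncorrected basis 442 is right and gives about 82%, but then 268 and 780 are not on that basis.

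This rests on the standard design effect for unequal clusters and the pooled two-proportion formula. The article does not show which route produced 442, so the defect lies in the justification, not in proven underpowering. Severity is moderate: no estimand, analysis or decision rule changes.

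**What to change.** Restate the paragraph on one named basis.

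- **(a)** Keep 268 and 780, say that they are continuity-corrected, and state that 442 patients in 34 practices with CV 0.5 give about 77% power, with 502 to 510 needed for 80%.
- **(b)** Say that 442 uses the uncorrected formula with CV 0.5, quote about 82% power, and restate the individual figure as 242 and the 20-practice figure as about 582 (600 at 30 per practice). The inflated 20-practice total would then be 600 × 1.3 = 780 in place of 1014.

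The choice should follow whichever calculation was actually run. The step from 442 to 576 can stay; at most, add that it tolerates a 23% loss. The cost is wording and a few recomputed numbers, with a less favourable stated power under (a). No extra enrolment is proposed.
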